## Abstract

**Introduction:**

Poverty is a key contributor to delayed diagnosis and limited access to early intervention and rehabilitation for children with cerebral palsy (CP) in rural Bangladesh. 97% of families of children with CP live below the poverty line in Bangladesh. Therefore, in low-and middle-income countries (LMICs), efforts to improve outcomes for children with CP (including health-related quality of life, motor function, communication, and nutritional attainments) should also include measures to improve family economic and social capital. We propose a randomised controlled trial (RCT) to evaluate the effectiveness of an integrated microfinance/livelihood and community-based rehabilitation (IMCBR) program for ultra-poor families of children with CP in rural Bangladesh.

**Material and methods:**

This will be a cluster RCT comparing three arms: (a) integrated microfinance/livelihood and community-based rehabilitation (IMCBR); (b) community-based rehabilitation (CBR) alone; and (c) care-as-usual (i.e. no intervention). Seven clusters will be recruited within each arm. Each cluster will consist of 10 child-caregiver dyads totalling 21 clusters with 210 dyads. Parents recruited in the IMCBR arm will take part in a microfinance/livelihood program and Parent Training Module (PTM), their children with CP will take part in a Goal Directed Training (GDT) program. The programs will be facilitated by specially trained Community Rehabilitation Officers. The CBR arm includes the same PTM and GDT interventions excluding the microfinance/livelihood program. The care-as-usual arm will be provided with information about early intervention and rehabilitation. The assessors will be blinded to group allocation. The duration of the intervention will be 12 months; outcomes will be measured at baseline, 6 months, 12 months, and 18 months.

**Conclusion:**

This will be the first RCT of an integrated microfinance/livelihood and CBR program for children with CP in LMIC settings. Evidence from the study could transform approaches to improving wellbeing of children with CP and their ultra-poor families.

## Introduction

Cerebral palsy (CP) is a group of non-progressive neurological disorders caused by damage to the developing brain [1]. The prevalence and severity of CP are considerably higher in low- and middle-income countries (LMICs) compared with high-income countries (HICs) [2–4] and diagnosis is likely to be delayed [3]. Early diagnosis of children with CP and access to evidence-based early interventions such as community-based rehabilitation (CBR) are key to improving the long-term health-related quality of life (HRQoL) [5], motor function [6], cognitive [7], and other health outcomes in children with CP. However, the majority of such evidence is from HICs [8, 9]. Randomised controlled trials (RCTs) testing the effectiveness of CBR programs for children with CP in LMICs are relatively scarce. Moreover, these interventions rarely consider issues pertinent in the lives of children with CP and their ultra-poor families in LMICs.

In LMICs, many families of children with CP are ultra-poor, which contributes to poor health care access, delayed diagnosis, delayed intervention, overall poor health and wellbeing, and long-term reduced effectiveness of rehabilitation therapies [3, 10–15]. Our last 16 years of research in rural Bangladesh, which led to the development of the Bangladesh CP Register (BCPR—first ongoing population-based CP register in LMICs) [16], confirms that diagnosis of CP is delayed [17] and there is limited or no access to evidence-based rehabilitation programs in rural Bangladesh [18]. The average age at diagnosis of CP in Bangladesh is 5 years compared to 1.5 years in HICs [2, 3]. We also found that even when rehabilitation programs were available, access to care was negatively impacted by poverty [3, 14]. In Bangladesh, 97% of families of children with CP live below the poverty line [3]. Moreover, people with disability and their families are often excluded from economic activities [19]. These families struggle to meet basic needs and their child’s rehabilitation often does not feature high on the agenda. Therefore, an integrated approach combining the physical rehabilitation of children with CP and the economic empowerment of their family is required for tangible long-term improvements.

Microfinance/livelihood support is an effective tool for improving economic, human (including non-cognitive skills), and social capital of disadvantaged people in LMICs particularly vulnerable groups such as women and children [20]. Microfinance/livelihood support programs can improve health by increasing financial access and service utilisation. Combining microfinance with health interventions has yielded promising results in the fields of HIV, malaria, and breastfeeding in Africa [21].

In addition, non-experimental and quasi-experimental studies testing the effectiveness of integrated health and economic interventions report significant improvements in reproductive and child health, nutrition, and immunisation [22, 23]. Non‐cognitive skills or soft skills are considered as important predictors of socio‐economic outcomes in life [24]. For instance, the training on soft skills (e.g. personal initiative) aided the development of small-scale businesses in the African context [25, 26]. Moreover, the interaction between diversified groups in society reduces prejudice and promotes inter‐group cooperation [27–29].

To be effective, interventions need to be tailored according to the needs of the target population [30]. Influential works by [name] Marmot, Chair of the World Health Organization (WHO) Commission on Social Determinants of Health, and others have demonstrated that socioeconomic factors are important determinants of health [31]. Even in HICs like the United Kingdom, the average life expectancy in poorer areas of Glasgow is about 20 years shorter than that for the rest of the country [32]. This gap can be explained as a direct result of poverty and related social disadvantage. Tangible improvements in the overall health status of people living in poverty can only be achieved by focusing on improving both health and economic/social capital. However, to our knowledge, no studies have examined the effectiveness of an integrated health and economic approach for children with CP and their families in LMICs.

In this paper, we describe an RCT protocol to test the effectiveness of an integrated microfinance/livelihood and CBR program (IMCBR) targeted to children with CP and their parents from ultra-poor families in rural Bangladesh. If the proposed integrated program is proved to be scientifically effective in improving the health and wellbeing of children with CP and their caregivers, the implementing NGO partner plans to scale up the program using existing connections with NGOs and microfinance organisations in Bangladesh, and in other LMICs where CSF Global is research active (e.g., Nepal, Indonesia, and Ghana).

## Materials and methods

### Study aims and objectives

This study aims to test the effectiveness of an “Integrated Microfinance/livelihood and CBR program” (IMCBR) among children with CP and their primary caregivers from ultra-poor families in rural Bangladesh. The program aims to improve the HRQoL, motor function, communication and nutritional status of children with CP; mental health, HRQoL and social capital of their parents; and socio-economic status (SES) and food security of their families.

Our specific objectives are;

To conduct an RCT with three parallel arms comparing (a) IMCBR, (b) CBR alone, and (c) care-as-usual (i.e. no intervention).To measure the effectiveness of IMCBR in improving the HRQoL, motor function, communication, and nutritional status of children with CP from ultra-poor families living in rural Bangladesh.To measure the effectiveness of IMCBR in improving mental health, HRQoL, and social capital of parents of children with CP living in rural Bangladesh.To measure the effectiveness of IMCBR in improving the SES of ultra-poor families of children with CP living in rural Bangladesh.

### Hypothesis

We hypothesise that compared to care-as-usual and CBR alone, the IMCBR program will be more effective in improving HRQoL, motor function, communication, and nutritional outcomes of children with CP from ultra-poor families; and the mental health, HRQoL, and social capital of their primary caregivers; and overall improvement in SES of the ultra-poor families of children with CP in rural Bangladesh.

### Overview of the study design

This will be a cluster randomised controlled trial comprising three arms. The unit of randomisation will be a cluster. This trial will incorporate two intervention arms in order to compare the usual rehabilitation services with a new integrated microfinance/livelihood and CBR services. Clusters randomised to intervention arms of the trial (i.e. IMCBR and CBR arms) will receive interventions following the protocol outlined in later sections. The interventions will be provided to dyads consisting of children with CP and their primary caregivers (Fig 1). Whereas clusters randomised to care-as-usual arm of the trial will not receive any active intervention.

**Fig 1 pone.0261148.g001:**
[figure not shown]
Study design (consolidated standards of reporting trials diagram).

### Study location

The study will be implemented in Shahjadpur sub-district (~324.15 sq. km) of Sirajganj district located in the northern part of Bangladesh. The study site is comprised of ~70,998 households with a total population of ~561,076 (child population aged 0–18 years ~226,114), and 12,117 live births per annum [3]. The study site constitutes a complex socio-demographic locale including urban, rural, and hard-to-reach areas and represents the overall socio-demographic and economic characteristics of rural areas in Bangladesh [33, 34].

### Recruitment of study participants

The study will utilise the BCPR as a sampling frame for participant recruitment. The BCPR is an ongoing surveillance of children with CP commenced in 2015 [3], and is currently being operated in four districts of Bangladesh. Between 2015 and 2019, 1125 children with CP have been registered into the BCPR from Shahjadpur (i.e. the study site) (study area–Fig 2). As part of this RCT, dyads of children with CP and their primary caregivers who meet the inclusion criteria will be recruited and assigned to different arms of the study.

**Fig 2 pone.0261148.g002:**
[figure not shown]
Geographic Information System (GIS) map of the study area and eligible clusters. This map was produced by the authors using ArcGIS Desktop 10.8 software.

### Inclusion/Exclusion criteria

Participants will be considered eligible for participation based on the following criteria:

Children with CP aged ≤5 years, from an ultra-poor family (as classified by the World Bank i.e. per day per capita income <1.90 USD; [35]) and registered in the BCPR. The BCPR registers children with CP following the case definition adopted from the Surveillance of CP in Europe (SCPE) and the Australian CP Register (ACPR) [3].Primary caregiver (e.g. parent, sibling, grandparent of the child with CP)Primary caregiver has the capacity to give informed consent and is willing to take part in the study including microfinance/livelihood arm along with their child with CP.

Participants will be considered ineligible for participation based on the following criteria:

Currently in receipt of microfinance/livelihood support from another source.Currently participating in any other clinical trial or intervention program.

The BCPR findings show that 34.2% of the children registered are aged <5 years and 97% of the families are ultra-poor [3]. Considering the number of registrants from Shahjadpur (i.e.~1125), there are ~373 children eligible to participate in the study. Therefore, recruitment of 210 children and their primary caregiver in the trial (<60% of the available pool) is feasible. Sociodemographic, economic, and health data of these children and their families are already recorded in the BCPR allowing quick identification and recruitment. All families enrolled in the BCPR have also been mapped using Geographic Information System (GIS) (Fig 2).

### Sample size calculation

The sample size for this cluster RCT has been computed based on methods described in Donner et al. [36]. We made several assumptions from the existing knowledge about the study population while calculating the sample size for this cluster RCT. Specifically, our sample size calculation is balanced between a standard statistical power and a pragmatic study setting. Based on our pilot data and existing literature we predict a 35% improvement of HRQoL in the IMCBR group, 20% improvement in the CBR alone group, and 5% improvement in the care-as-usual group [9]. A homogeneous study population will allow us to balance randomisation considering intra-cluster correlation of 0.5 and coefficient of variation in cluster size of 0.5.

Based on the calculation, we will recruit seven clusters in each arm (allocating 1:1:1), and each cluster will consist of 10 children with CP- primary caregivers dyads totalling 21 clusters of 210 dyads. With a sample size of 210 dyads, this study will have 80% statistical power to detect these effects (two-sided α-value = 0.05). Power calculation took into account up to 20% sample attrition by the end of the trial.

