### Statistical methods

Data will be collected using paper-based forms. Research data will be anonymised and stored securely and separately for participant identifiable information. This will include monitoring secure data transfer from field to central office, data entry and quality control of completed forms, query about missing or invalid data and archiving of physical forms. Data will be collected using validated questionnaires. Data will be entered using Microsoft Access or SQL Server as the relational database engine. Any error identified during data entry or in data cleaning will be logged for field supervisor assessment and will be resolved after proper field verification. The physical data will be stored for seven years in a locked cabinet at head office of CSF Global based in Bangladesh as per national and international guidelines.

For statistical analysis, we will import the dataset into Stata 17. Primarily, we will perform an intention-to-treat analysis. Since our primary endpoint (i.e. HRQoL) will have continuous data, we will perform a mixed effect model (e.g. generalised linear mixed model) to calculate the effect of intervention according to the components of TAPQoL. We will also compare the TAPQoL scores between the three arms, and assess the differences using appropriate tests. Our proposed models will include the intervention arm as a fixed effect and study samples in each cluster as a random effect to explain cluster effects. To account for the intra-cluster correlation in calculating 95% CI and p-value, we will use a Sandwich estimate of standard error.

Baseline characteristics will be compared (as part of data matching) and adjusted using appropriate regression models. Descriptive statistics (frequencies, means and 95% confidence intervals) will be used to describe the sample at baseline and post-intervention. All analyses will be conducted using a significance level set at p<0.05. Data visualisation will be done using R Studio version 4.1.0.

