## Results (pilot data)

We have piloted the activities of the proposed trial in the study area to determine the feasibility of the trial. The aim of the pilot study was to assess the acceptance rate and repayment rate of microfinance program among primary caregivers of children with CP. During the pilot phase, 20 ultra-poor families form the BCPR cohort (recruited between Jan 2015 and Nov 2018, n = 1,381) were identified who already have accessed microfinance from different local NGOs. The amounts of microfinance loan borrowed varied between ~100–300 AUD with 12-month loans payable in 45–46 weekly instalments. Of these families, the majority (n = 12) took loans to start/enhance income-generating activities (e.g. agricultural work, purchasing livestock, vehicle for hire, etc.). About 50% of borrowers repaid their first weekly instalment while the repayment schedule for the rest of the respondents was not due at the time of data collection.

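### The single 80% power figure for 210 dyads does not follow from the inputs printed with it: on a proportions reading every contrast falls far short, and on a mean-change reading it depends on an SD that is not given

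*Protocol article*

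**What the plan says.** The protocol article's Sample size calculation sets out the effects first: "we predict a 35% improvement of HRQoL in the IMCBR group, 20% improvement in the CBR alone group, and 5% improvement" in the care-as-usual group. It credits them to pilot data and existing literature. The clustering inputs are "intra-cluster correlation of 0.5 and coefficient of variation in cluster size of 0.5". The design is seven clusters per arm with 10 dyads each, and the test level is "two-sided α-value = 0.05". Up to 20% attrition is said to be allowed for. The conclusion is "With a sample size of 210 dyads, this study will have 80% statistical power to detect these effects". The section names no contrast for the 80%, and gives neither an SD nor a responder definition.

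Two other sections bear on this. Statistical methods begins its account of the primary analysis with "Since our primary endpoint (i.e. HRQoL) will have continuous data" and plans a mixed model. Results (pilot data) says: "The aim of the pilot study was to assess the acceptance rate and repayment rate of microfinance program". It describes 20 families who already held loans and reports no HRQoL result.

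**The concern.** An ICC of 0.5 is a very heavy clustering penalty: 70 dyads per arm shrink to about 10. It is hard to see how 80% power survives that for contrasts of 15 percentage points. One figure is also attached to three contrasts of different size (15, 15 and 30), and percentage improvements do not translate directly into the continuous analysis.

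The Hypothesis section expects IMCBR to beat both care-as-usual and CBR alone. IMCBR vs CBR is the contrast that isolates what microfinance adds. A reader who accepts 80% power would take a null result there as evidence of no added benefit, and the printed inputs do not justify that inference.

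**Working it through.** **Inputs** (all from Sample size calculation): 7 clusters per arm; m = 10 enrolled per cluster, or m = 8 after 20% attrition; ICC 0.5; CV 0.5; two-sided α 0.05; 35%, 20% and 5%.

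**Design effect.** DE = 1 + [(1 + CV²)m − 1] × ICC.
- m = 10: 1 + (1.25 × 10 − 1) × 0.5 = 6.75; effective n per arm = 70/6.75 = 10.4.
- m = 8: 1 + (1.25 × 8 − 1) × 0.5 = 5.5; effective n per arm = 56/5.5 = 10.2.

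**Reading 1: percentages are responder proportions.** This is the only reading that can be computed from the printed figures alone. With unpooled variance, power = Φ(|p1 − p2| / √{[p1(1 − p1) + p2(1 − p2)]/n} − 1.96), n = 10.37:
- 35 vs 20: 0.15/√(0.3875/10.37) = 0.776; Φ(−1.184) = 11.8%.
- 20 vs 5: 0.15/√(0.2075/10.37) = 1.060; Φ(−0.900) = 18.4%.
- 35 vs 5: 0.30/√(0.2750/10.37) = 1.842; Φ(−0.118) = 45.3%.

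Other variance choices and settings:

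| Setting | IMCBR vs CBR | CBR vs usual | IMCBR vs usual |
|---|---|---|---|
| ICC 0.5, CV 0.5, m = 10, unpooled | 11.8% | 18.4% | 45.3% |
| same, pooled | 11.3% | 17.1% | 39.3% |
| same, t on 12 df | 10.7% | 16.3% | 39.6% |
| ICC 0.5, CV 0.5, m = 8, unpooled | 11.7% | 18.2% | 44.6% |
| ICC 0.5, CV 0, m = 10, unpooled | 13.6% | 21.6% | 53.2% |
| ICC 0.05, CV 0.5, m = 8, unpooled | 32.2% | 53.4% | 94.5% |
| ICC 0, no attrition, unpooled | 52.2% | 78.7% | 99.8% |

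The stated 80% does not appear for any contrast at ICC 0.5. A one-sided test reaches at most 61%, and a global three-arm chi-square test 31–38%. Values near 80% arise only for single contrasts and only when stated inputs are dropped. One is the 78.7% in the last row. The other is 81.8% for IMCBR vs care-as-usual, if 0.5 is taken as a between-cluster CV of the outcome, the ICC is ignored and one cluster per arm is deducted. Treating 0.5 as a slip for 0.05 (an assumption) brings only IMCBR vs care-as-usual above 80%.

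**Reading 2: percentages are mean changes on the continuous score.** No SD is printed, so I assume the percentages are points and let the SD vary. Detectable standardised difference at 80% power = (1.96 + 0.84) × √(2/n):
- n = 10.37: 1.23, or 1.34 with 12 df.
- n = 10.18: 1.24, or 1.35 with 12 df.

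The largest SD compatible with 80% at m = 10 is therefore 15/1.23 = 12.2 for the 15-point contrasts (15/1.34 = 11.2 with 12 df), and 30/1.23 = 24.4 for the 30-point contrast (22.4 with 12 df).

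| Assumed SD (ICC 0.5, CV 0.5, m = 10, normal approximation) | 15-point contrast | 30-point contrast |
|---|---|---|
| 10 | 93% | >99% |
| 12 | 81% | >99% |
| 15 | 62% | >99% |
| 20 | 40% | 93% |
| 25 | 28% | 78% |
| 30 | 21% | 62% |

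At ICC 0.05 with 8 completers the detectable difference falls to 0.64 SD (0.69 with 12 df), so on this reading a slip in the ICC would matter a great deal.

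**The case against.** The strongest reply is that the endpoint is continuous by the protocol's own statement and no responder definition appears, so the proportion figures describe an analysis the trial does not plan. On the continuous reading 80% can be true: at ICC 0.5 an SD of about 12 points is enough for the 15-point contrasts. Baseline adjustment and repeated measurement would usually lower the residual SD further. A condensed article citing a named cluster-trial method may leave the SD to a fuller document.

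Much of this stands. A reader might infer that the trial has about 12% power for IMCBR vs CBR and is badly underpowered. The documents do not support that: it holds only if the percentages are proportions. The absence of an SD from an article is not itself a fault. A reader might also infer that the pilot never measured HRQoL. The article says only what the pilot aimed at and reports no HRQoL result, and existing literature is cited as a second source of the effects.

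What the reply does not do is support the sentence as printed. The article chose to print a specific ICC, CV, cluster number and cluster size, percentage effects and a resulting power. Read as proportions, those inputs contradict the result. Read as mean changes, the result rests entirely on a quantity that is not shown and would have to be fairly small at the stated ICC.

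**Conclusion.** The concern holds in a conditional form. The 80% figure is not reproduced by the printed inputs.

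- If the percentages are proportions, power at ICC 0.5 and CV 0.5 is about 11–12%, 16–18% and 39–45% for IMCBR vs CBR, CBR vs care-as-usual and IMCBR vs care-as-usual. IMCBR vs CBR is capped at about 52% whatever the ICC.
- If they are mean changes in points, power is undetermined. At ICC 0.5, 80% requires an SD of no more than about 12 points for the 15-point contrasts and about 24 for the 30-point contrast, slightly less with 12 df.

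These figures assume the standard unequal-cluster design effect and no variance reduction from baseline adjustment.

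Two lesser defects accompany this. Pilot data are cited for the HRQoL effects, but the pilot section reports only loan uptake and repayment. A cluster-size CV of 0.5 sits badly with a fixed 10 dyads per cluster, although CV 0 moves the unpooled proportion figures only from 12% to 14%, 18% to 22% and 45% to 53%.

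The statement should be corrected because it is the headline power claim for the primary outcome.

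**What to change.** Withdraw the blanket 80% statement. Restate power on the continuous TAPQOL score, separately for each of the three contrasts, giving:
- the mean difference and the SD;
- the ICC, confirmed or corrected, with results over a range of values;
- one cluster-size assumption (10 enrolled, 8 analysed);
- t-based degrees of freedom for 7 clusters per arm.

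If the planned size does not reach 80% for IMCBR vs CBR, say so and state the detectable difference. Do not put proportion-based power figures into the protocol, since no responder endpoint is defined. Cite the pilot as a source for the HRQoL effects only if it measured HRQoL; otherwise rely on the literature source alone.

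The cost is a rewritten section and possibly a less favourable stated power. No extra participants are needed.
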